## Methods/design

### Trial design

Through a pilot project in Aachen, this new form of care described here has already completed the phases of theory formation, modeling, and exploratory testing, including phase II in accordance with Campbell et al. [13] and feasibility testing or piloting in accordance with MRC (Medical Research Council) [14] under the name “Brückenschlag.” Within the follow-up project family-SCOUT, interventional levels described are now to be modeled in an appropriately complex evaluation design in order to test the benefits and appropriateness [15] and the degree of success of the intervention’s implementation. This study design combines elements of clinical effectiveness and implementation research in an effectiveness-implementation hybrid study type 2 [16]. The family-SCOUT effectiveness evaluation is based on a quasi-experimental, non-randomized control group design with two study arms (an intervention group (IG) and a control group (CG)), as well as one time point for preliminary measurement and two time points for follow-up measurements.

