### Participants

The study participants will be recruited consecutively in four regions over the recruitment period. Since the support structure in Aachen already existed due to the pilot project, it was ethically not reasonable to withhold the existing service from the patients there; thus, the other regions serve as the control group. In order to be able to depict the implementation of the intervention in another region, the allocation in Bonn was changed during the project. The control group was recruited in the first project phase (during the development of the intervention infrastructure) and the intervention group in the second phase (when the new supporting structures were available). Accordingly, participants in the control group had the option to switch to the intervention group later. In Aachen, the families will be recruited through the Center for Integrated Oncology (CIO) Aachen (CIO^A^, region 1). In Bonn, the families will be recruited through the CIO^B^ and through the Bonn Tumor Center (region 2). In Düsseldorf, the families will be recruited through CIO^D^, region 3) (Fig. 1). In addition, families will be recruited for semi-structured interviews in the Bad Oeynhausen region through the Specialist Clinic for Oncological Rehabilitation and Follow-up Rehabilitation in Bad Oexen (region 4).

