## Sample size

On the basis of the project’s pilot phase, it is assumed that 265 families can be included in region 1 (Aachen) in the intervention group (IG). In region 2 (Bonn), it is assumed that a total of 135 families can be included, with 70 families in the control group (CG) in the first year, followed by 65 families in the IG. In region 3 (Düsseldorf), an estimated total of 160 families can be included in the CG. This results in the following sample sizes: IG = 265 + 65 = 330; CG = 70 + 160 = 230. In total *N*=560 families should be included.

A HADS responder rate of around 30% between T0 and T2 is expected in the IG. With the planned sample size, a difference of 28% (IG) versus 16% (CG) will then be identifiable at the 5% significance level with a power of 90% in the full analysis population (after imputation for missing values for dropouts, 330 in the IG, 230 in the CG) using Fisher’s exact test. After exclusion of dropouts of 20% per group between T0 and T1 and again 20% between T1 and T2, sample sizes of 211 (IG) and 147 (CG) remain, such that a complete case analysis could detect a difference from 30 to 16% still with a power of 85%. For the semi-structured interviews, approximately 30–40 healthy partners will be recruited in regions 1–4.

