The primary analysis will be performed using the intention-to-treat principle being a conservative approach in superiority studies. Families enrolled in the CG in Bonn that claims great need for support will be analyzed as belonging to the CG. Only after the expiration of the study period, corresponding to approximately 12 months after inclusion (considering completion of T2 plus corresponding reminders), families may receive the intervention. The observation units will be the families, the parents, or the children. Cluster adjustment for families will be done, if appropriate. The primary analysis is the comparison of HADS response rates on the family level (MID ≥ 1.6 in at least one of the two parents) after 9 months between the IG and CG, using Fisher’s exact test. To adjust for potential confounders in this non-randomized trial, model-based secondary multiple regression analyses will be carried out for the following target variables on family level: HADS response in at least one parent, continuous HADS subscores for depression and anxiety separately for the healthy parent and parent with the disease, DT dichotomized for the cut-off point ≥ 5 for the healthy parent, PA-F-P-KF for the healthy partner, PCQ for the parent with the disease, FAD overall score and subscores for the family, and on children’s level KIDSCREEN for the children aged 8 and upwards. The sociodemographic and disease-specific variables will be included as confounders. Cluster adjustment according to the regions will take place using a corresponding random effect. Supplementary region-specific analyses will be carried out. Differences between the regions will be investigated using an extended interaction model with the independent variables of the region and interaction of the region with IG/CG. In the analysis of the KIDSCREEN questionnaire, the children (≥ 8 years old) will be the observation units, the adjustment will be made for the family cluster using additional random effects. The primary analyses will be carried out after the imputation of missing values of HADS at T0 and T2 by multiple imputations.

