### Limitations and generalizability

The study design is non-randomized and non-blinded. This might cause a bias between IG and CG, which could affect the main effect of the primary outcome. Differences in distributions of baseline variables between IG and CG will be discussed carefully. Some families that meet the inclusion criteria will not be included due to missing informed consent. Reasons for initial non-response will be documented. There might represent a selection bias in terms of greater enrolment of families who have time and resources to participate, although the outreaching time-flexible concept tries to counteract this. As the primary research data is based on a self-completion questionnaire survey, there might be a selection bias in terms of higher educated families with sufficient German language skills or without migration history. Families from the CG might be more likely to drop out than families from the intervention group, as a greater benefit can be expected there. At the time of inclusion, the affected parents may be at different stages of the disease. Patients may have been diagnosed with cancer only recently, and others may be post-recurrence, while another group may be in a palliative situation. Estimated effects and costs in the subpopulation with SHI data might be biased from this selection. In addition, the study recruits participants at four locations within Germany, which are located in immediate proximity, limiting the external validity. Caution should be applied with respect to generalizing the results.

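### Non-randomised comparison: the primary conclusion rests on an unadjusted Fisher test, while the adjusted model for the same endpoint is only secondary

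*Protocol article*

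**What the plan says.** The Trial design section describes a "quasi-experimental, non-randomized control group design with two study arms". The Participants section explains the allocation: because Aachen already had the service, "it was ethically not reasonable to withhold the existing service from the patients there; thus, the other regions serve as the control group". Bonn supplies both arms in sequence: "The control group was recruited in the first project phase (during the development of the intervention infrastructure) and the intervention group in the second phase". The Sample size section gives the arithmetic as "IG = 265 + 65 = 330; CG = 70 + 160 = 230", the terms being Aachen and Bonn for the intervention group (IG) and Bonn and Düsseldorf for the control group (CG).

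Under Statistical methods, "The primary analysis is the comparison of HADS response rates on the family level" at nine months by Fisher's exact test, after multiple imputation. Confounding is then taken up in a separate tier: "To adjust for potential confounders in this non-randomized trial, model-based secondary multiple regression analyses will be carried out". The first target listed for those regressions is HADS response in at least one parent, which is the primary endpoint itself. The region random effect is described with these regressions, not with Fisher's test.

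Two statements bear on the covariates. The opening paragraph of Statistical methods treats baseline variables that differ significantly as potential confounders. The later paragraph says sociodemographic and disease-specific variables will be included.

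The Limitations section states: "The study design is non-randomized and non-blinded. This might cause a bias between IG and CG, which could affect the main effect", meaning the effect on the primary endpoint. It adds that stage of disease at entry will vary, from recent diagnosis to palliative care. What it offers for baseline differences is careful discussion.

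**The concern.** Fisher's test holds its 5% level if families in the two groups would respond at the same rate without the intervention. Randomisation would justify that; allocation by region and phase does not. The test has no term for disease stage, baseline HADS, number of participating parents, region or phase.

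The plan already contains an analysis that addresses the measured part of this problem for the same endpoint, but it does not carry the primary conclusion. If the two analyses disagree, the plan as written makes the raw comparison decide. The abstract says the evaluation is meant to inform inclusion of the service in the statutory insurance catalogue, so the order matters.

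The covariate rule adds to this. Selection by baseline significance can miss a strong prognostic factor with a moderate imbalance and admit a weak one with a significant imbalance.

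**Working it through.** **1. The plan's own figures.** Exact power of the two-sided Fisher test, enumerating all 2×2 tables at alpha 0.05 (sidedness is not stated; two-sided is assumed and fits):

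- 330/230, 28% vs 16%: 91.7% (stated 90%).
- 211/147, 30% vs 16%: 86.0% (stated 85%).
- Dropout: 330 × 0.8 × 0.8 = 211.2 and 230 × 0.8 × 0.8 = 147.2.

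The sample-size figures are sound for an unadjusted Fisher test. The point is the choice of analysis, not the arithmetic.

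**2. How far group and region overlap** (Sample size section).

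- IG from a region without controls: 265/330 = 80%.
- CG from a region without intervention families: 160/230 = 70%.
- Families in a region with both arms: (65 + 70)/560 = 135/560 = 24%, and these are separated by phase.

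**3. Effect of a case-mix shift on the primary test.** Inputs: no intervention effect; CG response 16% (the plan's figure); the IG rate raised by an assumed shift through case mix alone. The documents give no size for the shift, so a range is shown. Rejection probability = sum, over tables with Fisher p ≤ 0.05, of Bin(x₁; n₁, 0.16 + shift) × Bin(x₂; n₂, 0.16).

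| Shift in IG (points) | 330/230 | 211/147 |
|---|---|---|
| 0 | 4.4% | 4.2% |
| 2 | 8.4% | 6.8% |
| 4 | 21% | 14% |
| 5 | 30% | 20% |
| 6 | 40% | 27% |

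The planned difference is 28 − 16 = 12 points, so shifts of 4 to 6 points are a third to a half of it.

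**4. What adjustment does for a measured factor.** Assume a binary factor present in 50% of IG and 30% of CG families, with response 30% when present and 10% when absent, and no intervention effect.

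- IG rate: 0.5 × 0.30 + 0.5 × 0.10 = 0.20.
- CG rate: 0.3 × 0.30 + 0.7 × 0.10 = 0.16.
- Fisher at 330/230 rejects in about 21% of trials. Logistic regression on group and the factor rejects in about 5% (simulation).

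**5. What adjustment does not do.**

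*Regression to the mean.* Assume two parents, a 0–21 score with mean 8, between-person SD 3.5, within-person SD 2.2, no intervention effect, and an IG baseline 0.5 points higher. Score reliability is 3.5²/(3.5² + 2.2²) = 12.25/17.09 = 0.72. If the excess is wholly transient, Fisher rejects in about 27% of trials (all scores drifting up 3 points) to 41% (no drift), and a model adjusted for both parents' T0 HADS still rejects in about 15% to 26%. If the 0.5-point gap is stable, Fisher stays near nominal and the T0-adjusted model slightly exceeds it, at about 7% to 8%.

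*Region.* With Aachen 5 points above Düsseldorf and Bonn midway at 16%, the IG rate is (265 × 0.185 + 65 × 0.16)/330 = 18.0% and the CG rate (70 × 0.16 + 160 × 0.135)/230 = 14.3%. Fisher rejects in 20%. Two of the three survey regions lie in one arm only, so only Bonn carries a within-region contrast. At 65 vs 70 families, 28% vs 16%, Fisher's power there is 35%, and phase still differs.

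**The case against.** The strongest reply is that the plan already deals with confounding. It has an adjusted model for this very endpoint, baseline comparisons, a region random effect, region-specific analyses and a region-by-group interaction model, and it states the risk of bias openly. A reader of the results will see both estimates. That is true, and it is why the remedy is modest. It does not change which analysis decides if the two disagree.

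The second reply is that adjustment is no cure. This also stands, as step 5 shows. It is a reason to state the limit, not a reason to leave measured confounders out of the primary analysis.

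The third is practical: 406 families had been assigned by September 2020, and the power statement is built on Fisher's test. Changing the primary analysis needs a fixed covariate list and a note on power, so it is more than a reordering on paper.

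Several stronger readings are tempting, and the documents do not support them:

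- *That the true false-positive rate is 27% to 41%.* Those figures need a wholly transient baseline excess. The upper one also needs response rates of about 52% and 60%, far from the planned 16% and 28%; the lower one needs a general 3-point rise in HADS.
- *That the change would cure clustering by region.* Assumed between-region correlations of 0.005 to 0.02 would put the error rate of Fisher's test at about 14% to 33%, but that is a limit of the design, not of the order of the analyses.
- *That control families join only a survey while intervention families join for support.* No passage says so, and Bonn controls may receive the intervention later.
- *That the cost-effectiveness ratio rests on the unadjusted contrast.* The Health-economic evaluation section names the primary outcome as its effect parameter and does not say whether the increment is adjusted.

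**Conclusion.** The concern holds as a weak choice of primary analysis in a design that the protocol itself calls open to bias. The text is explicit, so this is not a detail left to an unseen analysis plan. At the planned sizes and a control rate of 16%, a case-mix shift of 4 to 6 points would give a false positive in about 21% to 40% of trials. The shift is assumed: the documents give neither its size nor its direction, so the range illustrates and does not predict. With the adjusted model as primary, a measured confounder such as the one in step 4 is handled (about 21% falls to about 5%). Unmeasured confounding, the overlap of region with intervention and part of regression to the mean remain under either analysis.

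**What to change.** Before T2 outcomes are compared between groups, make the already planned adjusted model of family HADS response the primary analysis:

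- Fix the covariates in advance: at least disease stage or palliative status, T0 HADS of the participating parents, number of participating parents, and sociodemographic variables. Drop selection by baseline significance, and reconcile the two statements on covariates in Statistical methods.
- Pool over the imputations and report a standardised risk difference with a 95% confidence interval.
- Keep Fisher's test as the unadjusted supporting analysis.
- State with the conclusion that adjustment covers measured confounders only, cannot separate region from intervention, and only partly corrects regression to the mean.
- In the health-economic section, say whether the effect used in the ICER is adjusted.

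Cost: no new data beyond what the planned regressions already need. The downsides are some model dependence, a dated amendment to the primary analysis of a running trial, and a note to the power statement, which is calculated for Fisher's test.

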#### Statutory health insurance data

Statutory health insurance (SHI) data will be analyzed for all study participants who provided consent and are insured by one of the participating insurance providers. The data include master data, diagnostic data, and treatment data (type of treatment, with the date and costs) of outpatient care by physicians, in-patient care in hospitals, drugs and medication, rehabilitation, reintegration, domestic help, inability to work, domestic nursing care, and nursing services. SHI data covers the time period 12 months before intervention to the complete intervention time. Survey data will be linked with SHI data at the individual level for each respondent who has given consent for data linkage.

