## Statistical methods

Treatment groups will be described by their baseline variables. To investigate potential bias from non-randomization statistical tests corresponding to their distribution (Fisher’s test, *t* test, Wilcoxon test) will be performed to compare both groups. Baseline variables with significant differences will be considered as potential confounders in the following multiple regression analyses.

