The subpopulation with statutory health insurance (SHI) data will be investigated separately. The distribution of baseline variables will be compared between the subpopulations with and without SHI data. The target variables based on the SHI data will be analyzed descriptively and compared between IG and CG on individual level clusters adjusting for families. Costs and uptake will be analyzed in the health economic evaluation. Missing values for the clinical outcomes may arise due to dropouts (not filling the questionnaires at T0–T2, approx. 20% per group) or incomplete details.

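### The intervention-control comparison of health insurance outcomes names family clustering as its only adjustment, and no stated analysis uses the 12 months of pre-intervention insurance data

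*Protocol article*

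**What the plan says.** All references are to the protocol article.

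- **Design.** Trial design describes a "quasi-experimental, non-randomized control group design with two study arms". Under Participants and Sample size, Aachen supplies only IG families, Düsseldorf only CG families, and Bonn CG families first and IG families later.
- **Insurance data.** Statutory health insurance data states: "The data include master data, diagnostic data, and treatment data (type of treatment, with the date and costs"), and, on the window, "SHI data covers the time period 12 months before intervention to the complete intervention time".
- **Analysis of insurance outcomes.** Statistical methods: "The target variables based on the SHI data will be analyzed descriptively and compared between IG and CG on individual level clusters adjusting for families". The following sentence assigns costs and uptake to the health-economic evaluation.
- **Confounder adjustment.** The same section says: "To adjust for potential confounders in this non-randomized trial, model-based secondary multiple regression analyses will be carried out for the following target variables". It then names HADS response and subscores, DT, PA-F-P-KF, PCQ, FAD and KIDSCREEN. For these models, "The sociodemographic and disease-specific variables will be included as confounders". The rule for baseline imbalance is: "Baseline variables with significant differences will be considered as potential confounders in the following multiple regression analyses".
- **Costs.** Health-economic evaluation takes SHI costs from T0 to T2. It describes intention-to-treat analysis, multiple imputation, bootstrap intervals and a sensitivity analysis without families in which a parent died. It states no adjustment for earlier costs or for confounders.
- **Case mix.** Limitations and generalizability: "At the time of inclusion, the affected parents may be at different stages of the disease".

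**The concern.** The plan recognises confounding and says which outcomes receive adjustment for it. All of those are questionnaire outcomes. For SHI outcomes it describes a separate comparison whose one named adjustment, for family cluster, corrects standard errors for correlated relatives. That adjustment does not remove a difference between the groups that was there before enrolment.

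Such a difference is plausible. Two of the three regions that supply survey families feed one arm only, and the third switches arm by phase. Affected parents may be recently diagnosed, post-recurrence or palliative at entry. If one group used more care beforehand, and earlier use predicts later use, part of that difference would appear in the comparison and be read as an effect of the intervention. Person-level records of earlier use are already to be obtained, so the most direct control is available but has no stated role.

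At stake are the secondary SHI results and the incremental costs behind the ICER and ICUR. These belong to an evaluation that is meant to inform whether the service enters the statutory catalog.

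**Working it through.** **1. The plan's own figures.** No power or precision figure is given for SHI outcomes. The only figures are for the primary HADS test, and they reproduce. Exact two-sided Fisher power is 91.7% for 330 vs 230 at 28% vs 16% (stated 90%), and 86.0% for 211 vs 147 at 30% vs 16% (stated 85%). The complete-case sizes follow from 330 × 0.8 × 0.8 = 211 and 230 × 0.8 × 0.8 = 147. None of this bears on the SHI comparison.

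**2. Does any stated rule bring in confounders or earlier use?**

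| Provision | Reaches the SHI outcomes? |
|---|---|
| Baseline-imbalance rule | No. It feeds the regressions that follow it. |
| Confounder-adjusted regressions | No. The listed outcomes are all from questionnaires. |
| SHI comparison | Family clustering only. |
| Comparison of persons with and without SHI data | Addresses selection into the subpopulation, not IG against CG. |
| Health-economic evaluation | Costs from T0 to T2; no earlier costs or confounders named. |

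No stated analysis uses the 12 months before the intervention.

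**3. Size, by assumption.** Let *d* be the IG-CG difference in earlier use in SD units and *ρ* the correlation between earlier and later use. The documents give neither, nor the number of families linked. In a linear model with no true effect:

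- bias of the unadjusted contrast = *ρ* × *d*
- SE = √(1/n₁ + 1/n₂) in SD units, taking one person per family
- false-positive rate = P(|Z + *ρd*/SE| > 1.96)

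If half the planned families are linked, n₁ = 330/2 = 165, n₂ = 230/2 = 115 and SE = √(1/165 + 1/115) = 0.121.

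| *d* | *ρ* = 0.3 | *ρ* = 0.5 | *ρ* = 0.7 |
|---|---|---|---|
| 0.1 | bias 0.03; 5.7% | 0.05; 7.0% | 0.07; 8.9% |
| 0.2 | 0.06; 7.8% | 0.10; 13.1% | 0.14; 21.1% |
| 0.3 | 0.09; 11.5% | 0.15; 23.5% | 0.21; 40.9% |

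Worked cell (*d* = 0.3, *ρ* = 0.5): 0.15/0.1215 = 1.235, and P(Z > 1.96 − 1.235) + P(Z < −1.96 − 1.235) = 0.235. A simulation of 2,000 replicates for the *d* = 0.3 row gave 11.3%, 24.0% and 40.0% unadjusted, and 4.5%, 5.0% and 5.7% after adjustment for the earlier value.

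Over the same grid the range is 6% to 69% with all families linked (330 vs 230) and 5% to 27% with 30% linked (99 vs 69).

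**4. Precision.** Adjustment multiplies the residual variance by 1 − *ρ*². A contrast with 80% power then has power Φ((1.96 + 0.84)/√(1 − *ρ*²) − 1.96), which is 83.6%, 89.9% and 97.5% at *ρ* = 0.3, 0.5 and 0.7.

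**The case against.** The strongest reply is that the sentence on SHI outcomes fixes the unit of analysis and the clustering and excludes nothing. It is one line in a condensed article about a secondary, partly descriptive analysis, and covariates for such an analysis are often set in a fuller document. Asking for 12 months of earlier records may itself signal an intended baseline use. The sentence also gives no time window, and costs and uptake are sent to the health-economic evaluation. Finally, the limitations section promises careful discussion of baseline differences and warns that effects and costs in the SHI subpopulation may be biased by selection.

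Part of this stands. A reader might infer that the plan rules out covariates, or prescribes a comparison of post-enrolment values alone. The text says neither; the T0 to T2 restriction is stated only for costs in the health-economic evaluation. An unseen analysis plan may already add the missing terms.

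It does not dispose of the point. The article is not silent: it assigns confounder adjustment to a named set of outcomes, leaves SHI outcomes off it, and gives them a different and weaker adjustment. The health-economic section, to which costs are sent, has the same gap. Discussing imbalance is not adjusting for it, and the stated warning concerns selection into the SHI subset.

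**Conclusion.** The point holds as a weakness in the stated analysis of secondary outcomes. Followed as written, the IG-CG comparison of SHI outcomes and the incremental costs are open to confounding by earlier care use, although the data to reduce it are already to be obtained.

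The size is conditional. Bias arises only if the groups differ in earlier use and earlier use predicts later use. For *d* of 0.1 to 0.3 SD and *ρ* of 0.3 to 0.7 it is 0.03 to 0.21 SD, with a false-positive rate of about 6% to 41% if half the families are linked. These figures assume a linear model and one person per family; real costs are skewed and relatives are correlated. The correlation is probably lower for newly diagnosed patients.

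Three stronger readings are tempting, and the documents do not support them:

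- That the SHI results will be biased. No difference in earlier use and no correlation is given.
- That adjustment would restore a valid 5% test. It does so in step 3 only because earlier use is the sole confounder in that model. Region and phase would still be largely tied to group.
- That the trial's main conclusion is affected. The primary HADS test does not use SHI data.

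**What to change.** In Statistical methods, amend the sentence on SHI target variables so that the IG-CG comparison adjusts for the same person's value of that variable in the 12 months before T0, and for the sociodemographic and disease-specific confounders already named for the questionnaire models, with family clustering retained. T0 is a reference date that both groups have. Keep the unadjusted description and report earlier use by group beside it.

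In Health-economic evaluation, apply the same adjustment for earlier costs and confounders to the incremental costs.

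State in the limitations that confounding by region and phase may remain after adjustment. The form of the model, and whether patients, partners and children are fitted separately, can be left to the analysts.

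The cost is wording and modest extra modelling, since the earlier records are already within the planned data window. The one real addition is a rule for persons without 12 insured months before T0. If a fuller analysis plan already contains these terms, it is enough to align the two documents.
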